### Randomization

Participants will be randomly assigned in a 1:1:1 fashion to one of three arms: (1) high-dose, (2) low-dose, or (3) placebo. Randomization is based on computer-generated cards before study initiation and will be handed to authorized personnel in a sealed envelope. All study investigators and participants are masked to treatment allocation except investigational product (IP)-preparing personnel. The randomization schedule is not accessible except for safety reasons, until completion of this trial. Study drugs and the placebo are provided in an identical package.

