### Sample size estimates

The primary hypothesis of this study is that patients receiving Neu2000 before EVT will have an increased proportion of 3-month functional independence (mRS 0–2), compared with those receiving placebo. The expected proportions of functional independence are 41.6% and 70.0% in the placebo and Neu2000 groups, respectively. Such assumptions are based on the results of CT-based EVT trials (MR CLEAN [17] and ESCAPE [18]), and the preclinical Neu2000 research with transient occlusion model [9]. We chose the target sample size of 63 participants per group to provide 90% power, at a two-sided alpha of 0.05 to prove a treatment effect. The total sample size was determined to be 210 considering a 10% dropout rate for the primary endpoint.

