### Statistical analyses

The primary outcome analysis is based on the intention-to-treat principle. Statistical testing for the primary endpoint is conducted using the chi-square test for the comparison of functional independence among the three arms at a two-sided significance threshold of 10%. In case of significant differences, comparisons between the placebo and low-dose Neu2000 groups, and placebo and high-dose Neu2000 groups will be conducted. For secondary outcome analyses, the Cochran-Mantel-Haenszel test, the two-way analysis of variance test, and the chi-square test will be performed on the per-protocol population. In addition, multivariate analysis will be used to adjust for potential confounders, such as age, stroke severity, time to EVT onset, previous stroke, atrial fibrillation, diabetes mellitus, ASPECTS, and T-type internal carotid artery occlusion. If there are missing data despite best efforts to keep all missing data to a minimum, then missing outcome data will be not substituted for the primary outcome analysis.

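### The primary analysis is labelled intention-to-treat, but leaving missing 3-month mRS unsubstituted makes it a complete-case test, which can change the decision if effects are below plan or losses are uneven

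*Protocol article*

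**What the plan says.** All of this comes from the Protocol article.

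- **Statistical analyses, analysis principle:** "The primary outcome analysis is based on the intention-to-treat principle".
- **Statistical analyses, test:** a chi-square test for the "comparison of functional independence among the three arms at a two-sided significance threshold of 10" per cent, followed by each dose against placebo if that test is significant.
- **Statistical analyses, missing data:** if data are missing despite best efforts, "then missing outcome data will be not substituted for the primary outcome analysis".
- **Sample size estimates:** "We chose the target sample size of 63 participants per group to provide 90% power", and "The total sample size was determined to be 210 considering a 10% dropout rate for the primary endpoint".
- **Study outcome:** the primary endpoint contrasts mRS 0–2 with mRS 3–6 at 3 months, so a death is a scored outcome. The mRS is also a secondary outcome at 1 and 4 weeks.

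**The concern.** The label and the rule describe different sets of patients. Intention-to-treat is normally read as every randomised patient, analysed as allocated. The missing-data rule analyses only those with a 3-month mRS, and the sample size section already allows for one patient in ten having none.

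Two things are at stake. First, if patients who recover well or badly are more likely to be lost, the risk difference among completers is not the risk difference among those randomised. If that pattern also differs between arms, the test itself is distorted. Second, a patient with a mRS at 1 or 4 weeks but none at 3 months contributes nothing to the primary analysis, although the earlier score is informative and already collected.

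Enrolling 70 per arm to keep 63 protects power. It gives no protection against outcome-related or uneven loss.

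**Working it through.** **1. Reproduce the plan's figures.** Inputs from Sample size estimates: 41.6% and 70.0%, two-sided alpha 0.05, power 90%. With the mean rate (0.416 + 0.700)/2 = 0.558:

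n = [1.960·√(2·0.558·0.442) + 1.282·√(0.416·0.584 + 0.700·0.300)]² / 0.284² = 62.2, rounded up to 63.

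For dropout, 63/0.9 = 70 per arm and 3 × 70 = 210. Both figures reproduce. They imply 3 × 63 = 189 patients analysed and 21 left out (7 per arm if losses are equal).

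**2. When a complete-case analysis misleads.** Let the true success rate be p, and let successes and failures be retained with probabilities r₁ and r₀. The odds of success among completers are p·r₁ / [(1 − p)·r₀].

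- If r₁/r₀ is the same in every arm, it cancels. The odds ratio is unchanged, and equal arms remain equal, so the null test keeps its error rate. The risk difference still changes unless r₁ = r₀.
- If r₁/r₀ differs by arm, the test is distorted as well.

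**3. Effect on the plan's own test.** Three-arm Pearson chi-square, no continuity correction, 2 degrees of freedom, X² = Σ(O − E)²/E and p = exp(−X²/2), threshold 10%. Counts run placebo, then the two active arms. All counts and loss patterns are illustrative assumptions.

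*Full planned effect, 7 lost per arm*

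| Treatment of missing | Counts | p |
|---|---|---|
| Completers | 26/63, 44/63, 44/63 | 0.0008 |
| Missing as mRS 3–6 | 26/70, 44/70, 44/70 | 0.002 |
| Extreme: missing placebo all successes, missing active all failures | 33/70, 44/70, 44/70 | 0.094 |

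The decision at 10% holds in all three rows.

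*Smaller effect, 7 lost per arm*

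- Completers 26/63, 38/63, 38/63. Expected successes are 34 per arm and failures 29. The squared deviations are 64 + 16 + 16 = 96. X² = 96/34 + 96/29 = 6.13, p = 0.047.
- Suppose 4 of the 7 missing placebo patients and 2 of the 7 in each active arm were independent: 30/70, 40/70, 40/70. Expected successes are 36.67 and failures 33.33. The squared deviations sum to 66.67. X² = 66.67/36.67 + 66.67/33.33 = 3.82, p = 0.148.
- The difference from placebo falls from 12/63 = 19.0 points to 10/70 = 14.3 points, and the decision flips.

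*Uneven losses of 3, 9 and 9 (still 21 in all)*

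- Completers 28/67, 38/61, 38/61: p = 0.025.
- Missing as mRS 3–6, 28/70, 38/70, 38/70: p = 0.149. The decision flips.

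*Where the flip occurs with equal losses.* Holding placebo at 26/63 and giving both doses the same count, the extreme allocation reverses a significant result for every count from 37/63 to 43/63 per active arm. Counting missing as mRS 3–6 reverses only borderline results, such as 26/63, 36/63, 37/63 (p = 0.095 becomes 0.120).

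**The case against.** The strongest reply is that the label is defensible. The section states the principle and openly qualifies it, and intention-to-treat there may mean analysis as randomised, in contrast to the per-protocol set used for secondary outcomes. It is also a phase-II proof-of-concept trial with masked patients, treating physicians and assessors, which makes strongly arm-dependent loss less likely. This stands in part: it lowers the probability of distortion, but the rule still excludes randomised patients from the primary test.

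Four stronger readings are tempting and are not supported.

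- **That the missing patients overturn the result at the planned effect.** For one dose against placebo, 26/63 v 44/63 (28.6 points, p = 0.0013) can become 33/70 v 44/70 (15.7 points, p = 0.062). That crosses 5%, which is the sample-size alpha, while the threshold stated for the primary test is 10%. It is also the only one of the 64 possible allocations (8 × 8) that gives p above 0.05.
- **That a complete-case test is valid only if loss is unrelated to outcome.** Step 2 of the working shows that this is too strict for the null test.
- **That 10% of patients will be dropped.** Ten per cent is an allowance. Actual loss may be smaller or larger.
- **That the lack of a sensitivity analysis is itself a fault.** The full protocol and SAP are not shown and may contain one.

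**Conclusion.** The point holds as a mismatch between a stated label and a stated rule. It is not a gap left to the SAP: the article fixes the primary rule, and a later document could add to it but not replace it without contradicting this text.

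The size is conditional. Up to 21 of 210 randomised patients are excluded if loss reaches the allowance. At the full planned effect with equal losses, the three-arm decision at 10% is secure. For smaller effects or uneven losses it can flip, as in 0.047 to 0.148 and 0.025 to 0.149. Those examples assume particular completer counts and loss patterns unfavourable to the drug; they show what can happen, not what is expected. Nothing in the article indicates which way loss would run, so the direction of any bias is unknown.

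**What to change.** Before unblinding, replace the sentence on non-substitution with a primary rule that keeps all randomised patients. For example:

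- **Primary:** all randomised patients analysed as allocated. Missing 3-month mRS is multiply imputed by arm from age, baseline NIHSS, ASPECTS and whichever of the 1-week and 4-week mRS are available.
- **Sensitivity:** missing counted as mRS 3–6, and a tipping-point analysis.
- **Supportive:** the complete-case chi-square.

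Multiple imputation is one acceptable choice; what matters is that the rule is fixed in advance and covers everyone randomised. Patients lost early may lack the 4-week score, so the rule must work without it. If the sponsor prefers to keep the present test as primary, call it complete-case rather than intention-to-treat and add the same sensitivity analyses.

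The cost is a change of wording and modest programming, with no new data collection. The estimate may move in either direction.

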### Study organization and data monitoring body

The Steering Committee consists of local principal investigators, stroke neurologists, neuroradiologists, and neurointerventionists from each center, members of the Advisory Committee, and independent trial statisticians. The Trial Executive Committee consists of six principal investigators. Subcommittees exist for blinded-endpoint assessment, adverse event adjudication, and imaging analysis. All data will be entered into a web-based trial management system by trained local research nurses. The trial coordinator at the central trial office will carefully review and fully check all local data against source data.

## Discussion

The SONIC trial intends to show that Neu2000 before EVT can be safely administered and have a positive effect on tissue damage and clinical outcomes. Despite recent advances in EVT, considerable functional dependence (14–58%) still remains in patients with successful recanalization (60–90%) [2]. Ameliorating reperfusion injury is a possible target for new drug development; new drug trials are ongoing with uric acid, therapeutic hypothermia, and various neuroprotectants in EVT-attempted patients with stroke [3]. In addition, imaging findings according to the assigned groups will be informative in an effort to ameliorate reperfusion injury including edema and hemorrhagic transformation.

Our trial also intends to show that Neu2000 before EVT can be safely administered and have a positive effect on tissue damage and clinical outcomes in patients with acute ischemic stroke. This proof-of-concept trial will also show whether it would be more effective in specific clinical targets. In addition, this trial will investigate whether the escalating dose mitigates the ischemic damages shown in preclinical experiments [9]. Single-target neuroprotectants have failed in acute stroke clinical trials despite remarkable success in preclinical studies [19]. Multi-target neuroprotective strategy using Neu2000 is challengeable in its activity on timely blocking the sequential ischemic cascade, which is responsible for eventual neuroglial death after ischemic stroke (Fig. 1).

This trial is a novel study focusing on adjuvant neurovascular protection against ischemia-reperfusion injury in humans by selecting eligible patients as described above. Neu2000 is a first-in-class multi-target drug inhibiting NMDA-receptor-induced excitotoxicity, free-radical toxicity, and blood-brain barrier disruption. Future phase-III trials with solid evidence, like shift analysis, should be considered for establishing the neuroprotective properties in acute ischemic stroke.

## Trial status

This report describes the protocol, version 4.0, 19 June 2017. SONIC is currently recruiting study participants. The first patient was randomized in September 2016, and the targeted end date for recruitment is December 2018.

## Abbreviations

ASPECTS: Alberta Stroke Program Early CT score
BI: Barthel Index
EVT: Endovascular thrombectomy
IP: Investigational product
mRS: Modified Rankin Scale
NIHSS: National Institutes of Health Stroke Scale
NMDA: *N*-methyl-D-aspartate
SONIC: Safety and Optimal Neuroprotection of neu2000 in acute Ischemic stroke with reCanalization
